#### Blinding

Participants will be told that they will be randomly assigned to either acupuncture treatment or acupuncture-like simulation treatment and will be asked to wear an eye-patch when they receive treatment. Only the acupuncturists will know the group assignments. The participants and other researchers (including the data analysts, outcome assessors, and statisticians) will be blinded to group allocation. In order to ensure the successful implementation of the blinding method, all researchers will be trained before the trial begins.

#### Blinding success assessment

After the final treatment session, the success of blinding will be tested by asking the participants the following question “When you volunteered for the study, you were informed that you had an equal chance of receiving traditional acupuncture or acupuncture-like simulation treatment. Our study is finished now, which style acupuncture do you think you are received?” Three choices will be provided for participants: acupuncture treatment group; acupuncture-like simulation treatment group; and uncertain group. If participants choose “uncertain,” we will ask the reasons why they have made that assumption.

#### Safety and undesirable effects

Patients will be advised in the event of any undesirable effect after the application of acupuncture that they should discontinue acupuncture and contact their doctors; the doctor will diagnose and treat the adverse reactions. They will also be asked to contact the researcher who will have completed an undesirable effect form as well as the undesirable effect record log. Adverse events (AE) such as fainting, allergies, and pain may occur in acupuncture clinical trials [30]. If the participant faints, the needle will be immediately withdrawn. The patient will be returned to a supine position and given warm water or sugar water. The patient will be allowed to rest until they have made a full recovery. In the case of pain and allergies, the needle should be taken out immediately and treated according to the specific circumstances.

Any AE (include any discomfort, symptoms, or diseases occurring during the trial) will be reported by the patients and doctors after acupuncture treatment. All details of AEs will be reported in the CRFs. At the end of the study, we will analyze the influence of all events.

#### Data management

Patient characteristics will be recorded in CRFs, which will be stored in the researcher’s work office, and codes and initials will be used instead of the participants’ information to protect the participants’ privacy. Quality of CRF completion will be monitored by the specified researcher. All the original RCT data will be entered into the ResMan Research Manager of the Clinical Trial Management Public Platform. The relevant users will be trained and the system will be tested before it is officially launched to ensure that the system meets the trial requirements. Only relevant personnel will receive the account number and password once the system is officially launched. The clinical supervisor will monitor the work of the clinical trial center at least once a month.

### Statistical analysis

All data will be analyzed by intention-to-treat (ITT), including data from any participants who have dropped out of the RCT during the trial. All data will be entered twice by two different researchers to ensure the accuracy. If the data are found to be uncertain, the data supervisor will notify the researcher to respond with a data question form. If necessary, the statistician will send a data question form to the researcher and the researcher’s answer should be filled in the form. The question form is returned to the statistician by the inspector. The statistical analysis of data will be carried out by SPSS 23.0 software. Descriptive characteristics of baseline statistics will be reported as the mean ± standard deviation or median.

To analyze the primary outcome, the change of PSQI scores between baseline and week 8 will be calculated; comparisons between acupuncture group and sham-acupuncture group will be made using the Student’s t test. The rank-sum test is used for ranked data, while the 휒^2^ test is adopted to analyze categorical data. For other secondary outcomes, ISI, SAS, SDS, and MenQoL and Actigraphy assessments (TST and SA) between the two groups will be compared with the Student’s t test or the Wilcoxon rank-sum test. Analysis of secondary outcomes are considered exploratory; they were not part of the power calculations. All tests are two-tailed. *P* values ≤ 0.05 will be considered statistically significant.

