### Outcome measures

We will assess the primary outcome at baseline, week 4, week 8, after treatment, and with follow-ups at week 4 and week 12 after the end of treatment. Secondary outcomes will be assessed at baseline and week 8.

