#### Sample size

The sample size calculation was based on the change of PSQI scores. Systematic review [21] shows that at least a 2.70-point difference in PSQI scores between acupuncture and sham acupuncture has clinical significance. We expected that acupuncture would outperform the sham acupuncture by 3 points; therefore, a sample size of 35 participants should be recruited in each group. Considering a dropout rate of ~ 20%, each group will take 42 cases. Therefore, a total of 84 participants should be recruited for this RCT.$$\mathrm{N}=2\ast \kern0.5em {\left[\frac{\left({U}_{\upalpha}+{U}_{\upbeta}\right)\upsigma}{\updelta}\right]}^2;\kern0.5em \left(\upalpha =0.05,\upbeta =0.2\right)$$

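### The plan promises an ITT analysis that includes dropouts, but the primary t test on week-8 PSQI change can use only participants with a week-8 score and so defaults to an available-case analysis

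*Protocol article*

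**What the plan says.** The Statistical analysis section of the protocol article sets the population: "All data will be analyzed by intention-to-treat (ITT), including data from any participants who have dropped out of the RCT during the trial". For the primary outcome it then states that "the change of PSQI scores between baseline and week 8 will be calculated" and that "comparisons between acupuncture group and sham-acupuncture group will be made using the Student’s t test". It adds: "All tests are two-tailed".

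More PSQI data are planned than this test uses. Outcome measures says "We will assess the primary outcome at baseline, week 4, week 8, after treatment", followed by two follow-up assessments at 4 and 12 weeks after treatment ends. Table 1 agrees.

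The Sample size section gives the target, "We expected that acupuncture would outperform the sham acupuncture by 3 points", and the benchmark, "at least a 2.70-point difference in PSQI scores between acupuncture and sham acupuncture has clinical significance". It asks for 35 participants per group and raises this to 42 for a dropout rate of about 20%.

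Two other places bear on who will have a week-8 score. Under Safety and undesirable effects, participants with an undesirable effect are told that "they should discontinue acupuncture and contact their doctors". The Discussion says that follow-up interviews will be held by phone to record outcomes.

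**The concern.** The population statement and the named test do not fit together for a participant with no week-8 PSQI. Such a person has been randomised and has a baseline score, perhaps a week-4 score too, but has no change to week 8. A two-sample t test on that change leaves the person out, whatever the population is called. Even if the ITT sentence means only that the data dropouts did provide will be used, this test has no place for them.

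A comparison of those who happen to have a week-8 value is no longer protected by randomisation. If the people lost differ in outcome from those who stay, and differ in another way in the other arm, the estimated effect shifts. That is conceivable here, because one arm has needle insertion, manipulation and electrical stimulation while the other has none of these. The week-4 PSQI, which carries information on how those people were doing, plays no part in the stated primary analysis.

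**Working it through.** **1. What the sample size implies.** Inputs from the Sample size section are 35 per group, about 20% dropout and 42 per group.

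- The dropout step reproduces as 35 × 1.2 = 42. Dividing by the retained fraction gives 35 / 0.8 = 43.75, that is 44; the difference is minor.
- Going from 42 back to 35 is a loss of 7 / 42 = 16.7%. A full 20% loss leaves 42 × 0.8 = 33.6 per group.
- The 35 itself cannot be reproduced because no SD is stated. Solving the section's formula for a two-sided alpha of 0.05, 80% power and a difference of 3 gives an SD of 3 × √(35/2) / (1.960 + 0.842) ≈ 4.48. Any SD from about 4.42 to 4.48 rounds up to 35. This SD is an assumption and is used only in the next line.
- At that SD, the normal approximation gives 80% power with 35 per group, 78–79% with 33–34, and 87% if all 42 contribute.

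Two things follow. The sizing treats dropouts as adding nothing to the primary test, which is the available-case reading and not the ITT sentence. And the loss of precision at 20% dropout is small, so bias is the issue rather than power.

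**2. Size of a possible bias.** Let *f* be the fraction of the acupuncture arm without a week-8 PSQI, and let those people improve by *g* points less than the completers in that arm. Let sham non-completers be like sham completers. With completer mean improvement *m*, the mean over everyone randomised to acupuncture is

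(1 − f) × m + f × (m − g) = m − f × g.

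The available-case difference therefore exceeds the all-randomised difference by f × g. No SD is needed. The values of *f* and *g* are assumptions. Each cell gives the bias and, in brackets, the all-randomised difference behind an available-case difference of 3.

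| Missing, f | g = 1 | g = 2 | g = 3 |
|---|---|---|---|
| 10% | 0.10 (2.90) | 0.20 (2.80) | 0.30 (2.70) |
| 16.7% | 0.17 (2.83) | 0.33 (2.67) | 0.50 (2.50) |
| 20% | 0.20 (2.80) | 0.40 (2.60) | 0.60 (2.40) |

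**3. A second illustration.** If every non-completer in both arms had zero change, with the same *f* in each, an available-case difference of 3 would become 3 × (1 − f): 2.7 at 10%, 2.5 at 16.7% and 2.4 at 20% missing.

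**4. Yardstick.** The planned effect minus the stated clinical threshold is 3 − 2.70 = 0.3 points. Several cells above reach or exceed that.

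**The case against.** The strongest reply is that only a condensed article is at hand. Rules for missing values are commonly left to a statistical analysis plan or full protocol, and their absence here is no fault. ITT says who is analysed and in which arm, while a t test says how the arms are compared. The two agree if week-8 scores are obtained after treatment stops or are imputed. This stands in part: the lack of an imputation rule is not the point. What remains is that the article commits to a population, an endpoint and a test that do not fit for those without a week-8 score, and sizes the trial as though those people drop out of the analysis.

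A reader might infer more: that the primary result will be a completer analysis, with 20% missing at week 8 and unequal loss by arm. The documents do not support that.

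- The 20% is a planning allowance for dropout with no timing, in a trial followed to 12 weeks after treatment. Some of it may fall after week 8.
- Advice to stop acupuncture concerns treatment, not assessment. PSQI is self-rated, phone interviews are planned, and the 200 RMB subsidy is paid after the follow-up assessments. Someone who stops treatment may well give a week-8 score.
- No figure in the article shows that undesirable effects or losses will be more frequent under acupuncture.
- The bias depends on assumed values of *f* and *g*. If loss acted alike in both arms it would cancel, and if sham non-completers did worse it could reverse.

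It is also fair to say that a week-8 change score is a legitimate endpoint, and that a repeated-measures model does not deliver full ITT either. Of the 18 sessions, 3 × 4 = 12 fall in the first four weeks, and anyone lost before the week-4 PSQI contributes no post-baseline score.

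**Conclusion.** The point holds as a mismatch between the stated population and the stated primary test. As written, the test uses only participants with a week-8 PSQI, defaults to an available-case analysis, and ignores the baseline and week-4 scores of those lost.

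The consequence is a risk of bias of roughly 0.1 to 0.6 PSQI points. It rests on three assumptions: 10–20% missing in the acupuncture arm, non-completers there improving 1–3 points less than completers, and sham non-completers no different from completers. The upper part of that range exceeds the 0.3 points between the planned effect and the 2.70 threshold. The test itself is against no difference, so the shift matters most for whether the estimate is read as clinically relevant. Neither the occurrence nor the direction of bias can be established from the article.

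**What to change.** Keep the week-8 endpoint and change the primary analysis to a mixed model for repeated measures on the post-baseline PSQI scores already scheduled, at least weeks 4 and 8. Include treatment, visit, treatment-by-visit, baseline PSQI and baseline-by-visit terms, with an unstructured covariance. Name the treatment contrast at week 8 as primary. The model uses the week-4 score of someone with no week-8 score, and is valid if loss depends only on observed scores.

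Two additions are needed:

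- State that PSQI is still collected, by phone if necessary, from participants who stop treatment. Time the call to week 8, because the questionnaire asks about the past month.
- Add one sensitivity analysis under missing-not-at-random, for example delta-adjusted or reference-based imputation. It should also cover those lost before week 4, whom the model cannot recover.

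Settle this before unblinding, so that the missing-data method cannot be chosen with results in view. If an unseen analysis plan already contains such a method, the article's primary-analysis text should be brought into line with it.

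The cost is revised wording and modest programming in the SPSS software already planned, with no new visits. The downside is analysis and reporting slightly more complex than a t test.

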### Inclusion criteria

Participants with the following conditions will be included:Menopausal women aged 45~60 years;Participants who meet the diagnostic criteria of TCM in accordance with the above perimenopausal and insomnia [22];Participants in line with the international classification of sleep disorders (ICSD-3) for the diagnosis of insomnia;Participants whose PSQI score is > 5;Participants who voluntarily agree to join the study and to sign the written informed consent form for the randomized controlled trial (RCT).

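### The primary t test on PSQI change is valid but does not adjust for baseline PSQI; ANCOVA would be at least as precise at no cost

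*Protocol article*

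**What the plan says.** The Statistical analysis section of the protocol article defines the primary endpoint in these words: "To analyze the primary outcome, the change of PSQI scores between baseline and week 8 will be calculated". The test follows in the same sentence, with no model around it: "comparisons between acupuncture group and sham-acupuncture group will be made using the Student’s t test". The section adds that "All tests are two-tailed". Neither that section nor any other names a covariate, an ANCOVA or a regression model.

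Baseline PSQI will be available for everyone. Table 1 schedules it, and Outcome measures says "We will assess the primary outcome at baseline, week 4, week 8, after treatment, and with follow-ups at week 4 and week 12". The entry rule on the same scale is "Participants whose PSQI score is > 5".

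The Sample size section uses the same variable as the test: "The sample size calculation was based on the change of PSQI scores". Its target is "We expected that acupuncture would outperform the sham acupuncture by 3 points", with alpha 0.05 and beta 0.2, and it concludes that "a sample size of 35 participants should be recruited in each group", raised to 42 for dropout. The formula contains sigma, but no value for it is printed.

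**The concern.** A change score uses the baseline by subtracting all of it, which amounts to assuming that each extra baseline point predicts exactly one extra point at week 8. ANCOVA estimates that slope from the data. Both methods estimate the same treatment effect in a randomised trial. They differ in precision whenever the true within-group slope is not 1.

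Two things are at stake. One is power and interval width in a trial sized at 80% power for a 3-point difference. The other is stability of the estimate: if the arms differ by chance at baseline, the change-score difference is shifted by that imbalance times (slope − 1). Randomisation is in blocks of six and the article describes no stratification by severity, so the design does not control this imbalance either.

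Because the protocol names the primary test outright, this is a stated choice and not a detail left to an analysis plan.

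**Working it through.** **Inputs from the protocol article:** difference 3 points, two-sided alpha 0.05, power 80%, 35 per group before dropout, 42 after.

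**Inputs assumed (not in the document):** the correlation r between baseline and week-8 PSQI, and the ratio of the baseline SD (s0) to the week-8 SD (s1).

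**Step 1: the plan's own figure.** The printed formula is n = 2[(Uα + Uβ)σ/δ]². Sigma is not given, so 35 cannot be reproduced forwards. Solving backwards, σ = 3 × √(35/2) / (1.960 + 0.842) = 4.48. I take this as the SD of change. For the planned t test at 35 per arm (68 df), the noncentrality is 3 / (4.48 × √(2/35)) = 2.80 and power is 78.9%.

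**Step 2: relative precision.** Per patient, the variance of change is s0² + s1² − 2·r·s0·s1, and the ANCOVA residual variance is s1²(1 − r²). Their ratio is

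Var(ANCOVA) / Var(change) = s1²(1 − r²) / (s0² + s1² − 2·r·s0·s1).

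The within-group slope is r·s1/s0, and the ratio equals 1 only when that slope is 1. With s0 = s1 the ratio simplifies to (1 + r)/2.

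**Step 3: power at 35 per arm**, difference 3, change SD 4.48, with one df given up for the covariate (67 df):

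| s0/s1 | r | slope | variance ratio | power, ANCOVA | power, t test |
|---|---|---|---|---|---|
| 1 | 0.3 | 0.30 | 0.65 | 93% | 79% |
| 1 | 0.5 | 0.50 | 0.75 | 89% | 79% |
| 1 | 0.7 | 0.70 | 0.85 | 85% | 79% |
| 0.75 | 0.3 | 0.40 | 0.82 | 86% | 79% |
| 0.75 | 0.5 | 0.67 | 0.92 | 82% | 79% |
| 0.75 | 0.7 | 0.93 | 1.00 | 79% | 79% |

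Worked example for the fifth row, with s1 = 1 and s0 = 0.75: 0.75 / (0.5625 + 1 − 0.75) = 0.75 / 0.8125 = 0.92.

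In the equal-SD rows the gain is worth 1/0.65 − 1 = 54%, 1/0.75 − 1 = 33% and 1/0.85 − 1 = 18% more patients. In the last row it is nil.

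**Step 4: chance imbalance.** A 1-point baseline difference shifts the change-score estimate by (1 − slope) points in size. In the equal-SD rows that is 0.7, 0.5 and 0.3 points, or 23%, 17% and 10% of the 3-point target. In the last row it is 0.07 points.

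**The case against.** The strongest defence is that nothing here is an error. A t test on change is unbiased under randomisation, holds its type I error, and matches the variable behind the sample size. Baseline PSQI is used, through subtraction. All of that stands. The point is therefore about efficiency, and a reader should not infer that the planned test is biased or invalid.

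A reader might also infer three stronger things that the document does not support.

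- *That precision is lost whenever the correlation is below 1.* The governing quantity is the slope, r × s1/s0. Entry requires a PSQI above 5, which truncates the baseline but not week 8, so s1 may exceed s0. The slope can then be close to 1 with r well below 1, as in the last row of the table.
- *That baseline PSQI will vary widely.* The entry rule is a restriction, and no baseline SD is reported.
- *That the trial has no reserve.* Forty-two per arm are recruited and the analysis is by intention to treat. If all 42 contribute week-8 data, t-test power with the same SD is 86%. The 79% applies when only 35 per arm are analysed.

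The power figures also rest on a back-solved SD, and both r = 0.7 rows fit the scale poorly. With equal SDs, r = 0.7 implies a baseline SD of 4.48/√(2 × 0.3) = 5.78, more than the 4.61 of a uniform spread over scores 6 to 21. With s0/s1 = 0.75, it implies a week-8 SD of 4.48/√0.5125 = 6.26, close to a uniform spread over 0 to 21. So the rows with the smallest gain in each block are not the most natural ones if 4.48 is right, but 4.48 is itself an inference.

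None of this removes the case for adjustment: apart from one degree of freedom, ANCOVA is never less precise than the change score.

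**Conclusion.** The point holds as a recommendation on efficiency. The protocol commits the primary analysis to an unadjusted t test on change. That test is valid, but it is less precise than a baseline-adjusted comparison unless the within-group slope is 1, and it leaves the estimate exposed to chance baseline imbalance.

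The reduction in variance lies between almost none and about a third (ratios 1.00 to 0.65). This range rests on assumed correlations of 0.3 to 0.7 and assumed SD ratios of 1 and 0.75; the power figures also need the back-solved change SD of 4.48. That the unadjusted choice was made is certain. How much it costs cannot be settled from the document.

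**What to change.** In the Statistical analysis section, replace the primary test with an ANCOVA of week-8 PSQI (or, equivalently for the treatment effect, of change) on treatment group with baseline PSQI as covariate. Test at two-sided 0.05 and report the adjusted mean difference with its 95% CI. Keep the t test on change as a sensitivity analysis.

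The cost is about one sentence. The SPSS software already named fits this model, baseline PSQI is already collected, and the sample of 84 need not change. The Trial status section describes the trial as still in preparation, so on that account the change can be specified before data exist. Doing the same for the secondary outcomes is optional, because the protocol labels those analyses exploratory.

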### Monitoring

To improve the quality of this RCT, the whole process will be conducted under the supervision of a qualified clinical trial expert and be carried out by Shanghai Municipal Hospital of Traditional Chinese Medicine. The Clinical Research Center of Drugs of the Shanghai University of Traditional Chinese Medicine will provide data monitoring with access to any interim results and will make the final decision to terminate the trial if necessary. It also identify problems in the project, if any; the center makes the decisions to change the details of this protocol and announce the persons conducting the trial by written notice after approval by the application ethics committee. In addition, a qualified clinical trial expert will be invited to monitor this study and the PI will take full responsibility and will make the final decision.

## Discussion

Acupuncture treatment has been practiced in China for more than two millennia [31] and in recent years has been widely used in Western countries [32]. Recent studies have found that acupuncture can be used to relieve vasomotor symptoms during the MT [23], but have not yet established the effects of acupuncture on insomnia during the MT. This is a valuable clinical RCT aimed at treating insomnia in menopausal women. We use acupuncture and sham acupuncture [33] to evaluate the efficacy of acupuncture on improving sleep quality. In addition, we use a strictly RCT, utilizing the control group method to reduce test bias and ensure the reliability of the RCT.

The improvement on previous trials offered in this RCT is the method of point selection. Individualized treatment upon syndrome differentiation is the basis of TCM theory [23]; the selection of points is a question for the world acupuncture researchers [34]. To give some evidence for the effects of treatment upon syndrome differentiation, we set eight points as main points and add two acupoints based on individual differences in the syndromes. Another advantage is the use of Actigraphy. This wrist-worn sleep monitor can provide an objective assessment for the treatment effect [35]. This is very useful for us to compare and evaluate the change of patients’ sleep quality before and after treatment.

Another innovation in this trial is the design of the treatment frequency. In the first month, we will give full dose (three times per week) treatment. After the first month, we will decrease the frequency of the acupuncture treatment. This will be beneficial for us to observe the acupuncture therapeutic effect and to achieve the purpose of maintaining the minimum therapeutic dose in the long term.

However, this RCT still faces some challenges. First, the single-blinded method. For clinical trials of acupuncture, it is inevitable that acupuncturists know about the acupuncture treatment or sham acupuncture treatment. All participants will be asked to wear an eye-patch and will be arranged in a separate quiet space during the treatment. Second, the application of the sham acupuncture method. The acupuncturists will receive several sessions of strict training before the study begins to ensure the proper sham acupuncture techniques. Finally, the challenge of participant compliance. We will provide patient outreach over the phone to arrange the treatment time reasonably and to improve the attendance rate of the patients. The researchers will conduct follow-up interviews by phone to record patient outcomes.

To achieve our clinical goals, we will strive to standardize every step of the study, including acupoints selection, acupuncture operation, needle apparatus, and therapists’ clinical experience. We expect that this trial will provide strong positive evidence for acupuncture treatment of sleep disorders in the perimenopausal period.

